**Objective:**

The purpose of this protocol is to describe the rationale and methods for a nonrandomized, single-arm trial assessing objective and subjective sleep quality in community-dwelling older adults aged 60-80 years with synchronous sleep patterns and sleep appraisal compared to those in older adults with asynchronous sleep patterns and sleep appraisal. The trial will further examine the role of cognitive, behavioral, and hyperarousal processes in mediating the treatment outcomes of web-based CBT-I.

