The concurrent measurement of objective and subjective sleep quality will be used to determine the prevalence of individuals with asynchronous sleep patterns and sleep appraisal in this sample (phase 1). Phase 2 will assess the impact of a web-based CBT-I program on the sleep outcomes of individuals with synchronous sleep patterns and sleep appraisal and those with asynchronous sleep patterns and sleep appraisal. It is anticipated that complaining good sleepers and complaining poor sleepers will show improved sleep outcomes following CBT-I, compared with noncomplaining good and poor sleepers. We further hypothesize that individuals with a sleep complaint but without poor sleep quality (complaining good sleepers) experience higher levels of dysfunctional sleep cognitions and distress than persons with poor sleep in the absence of a sleep complaint (noncomplaining poor sleepers). We expect that additional factors such as hyperarousal [35], sleep effort [36], sleep-related self-efficacy [37], sleep locus of control [38], sleep-related behaviors [39], and chronotype [40] mediate the relationship between web-based CBT-I and sleep outcomes in older adults; therefore, these processes will also be examined.

Since our planned study is likely to generate a considerable amount of data, we aim to reduce publication bias and improve the reproducibility of our research by publishing this research protocol.

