### Design

Study participants will be required to complete a web-based questionnaire battery at baseline and following the intervention. It is estimated that it will take approximately 20-25 minutes to complete the questionnaire battery. Sleep-related dysfunctional beliefs will be assessed using the Dysfunctional Beliefs and Attitudes about Sleep (DBAS-16) scale [42]. The DBAS-16 was developed to examine sleep-related cognitions and dysfunctional beliefs. Items such as “I am worried that I may lose control over my abilities to sleep” are scored on a 10-point Likert scale ranging from 0 to 10. Like the original 30-item version, the DBAS-16 has been found to reliably discriminate between self-reported good and poor sleepers in older adult populations with adequate internal consistency (Cronbach α=.79 for research samples). A DBAS score of 4 or above is indicative of a clinically significant level of dysfunctional beliefs around sleep [21].

The Pittsburgh Sleep Quality Index [43] consists of 19 items and examines sleep quality and disturbances over the past month. The first 4 questions are open, whereas items 5 to 19 are rated on a 4-point Likert scale. Individual item scores from the 7 sections are calculated first, and those 7 component scores are subsequently added up to calculate the global score ranging from 0 to 21. A sleep score of >5 is indicative of poor sleep quality. The Pittsburgh Sleep Quality Index measures sleep quality in a broader sense than just insomnia severity and has good internal consistency (Cronbach α=.83).

The Insomnia Severity Index [44,45] is a brief self-report questionnaire used to measure the severity of insomnia, impairment of daytime functioning, and worry about sleep over the past 2 weeks. It examines both nighttime and daytime components of insomnia and is increasingly used in research as an instrument to examine treatment response. The Insomnia Severity Index has been shown to have excellent internal consistency in community samples (Cronbach α=.90).

The Glasgow Sleep Effort Scale [36] reviews sleep effort. Sleep effort is a concept that explains a person’s voluntary effort to control a partially involuntary process, namely falling asleep. The Glasgow Sleep Effort Scale consists of 7 items, for example, “I put too much effort into sleeping when it should come naturally,” rated on a 3-point scale (“very much”, “to some extent”, and “not at all”). Internal consistency was reported as fair, with Cronbach α=.77 [36].

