Following the baseline assessment, including the recording of demographic information and sleep complaints, the administration of the questionnaires, and actigraphy measurement, all groups will receive identical instructions for the web-based CBT-I program. Participants will be required to complete the 4 sessions plus homework of the program within 4 weeks. Participants will receive weekly email reminders from the principal investigator to confirm the completion of each of the 4 CBT-I modules. Once the completion of the CBT-I program has been confirmed with the participant, actigraphy, sleep diary, and questionnaire measurements will be repeated posttreatment. The study process is shown in Figure 1.

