### Statistical Analysis

An a priori power analysis using the program G*Power was performed to assess whether the study will have enough power to detect significant differences in sleep outcomes between the study groups [60]. We calculated that a sample size of 40 would be sufficient to detect this size effect. In order to account for attrition rates and missing data, a minimum of 60 participants will be recruited for the study.

Since sleep complaint status (sleep problem, eg, initial insomnia, for a minimum of 6 months) is used to classify participants as complaining or noncomplaining sleepers, multivariate ANOVA will be conducted separately to examine subjective and objective sleep quality for the 4 sleep groups. The multivariate ANOVA enables the analysis of multiple continuous dependent variables simultaneously (eg, sleep onset latency, wake-after-sleep onset, total sleep time, and the number of nighttime awakenings). In addition, a mediation analysis will be performed to determine whether sleep improvements following web-based CBT-I are the result of changes in sleep-related beliefs or other factors in older adults living in the community. Mediation analysis will be carried out using the bootstrapping method in the Hayes Process Macro for mediation, moderation, and conditional analysis for SPSS (version 28.0; IBM Corp) [61,62].

Actigraphy measures will be scored using the Cole-Kripke algorithm, which is suitable for use with older populations [63] and using ActiLife software (ActiLife 6 software, Version 6.13.1, ActiGraph). The autoscored data will be manually compared with the sleep diary to determine any incongruence between the actigraph measurements and the sleep diary.

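### The mediation aim claims that sleep improves after CBT-I because beliefs change, but one arm measured at two shared occasions can show only that the changes are associated

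*Protocol article*

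**What the plan says.** The Abstract's Objective describes a "nonrandomized, single-arm trial". Under Procedure, "all groups will receive identical instructions for the web-based CBT-I program". No untreated, waitlist or alternative-treatment comparator is described.

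The Introduction expects that factors including hyperarousal, sleep effort, self-efficacy, locus of control, sleep-related behaviors "and chronotype [40] mediate the relationship between web-based CBT-I and sleep outcomes in older adults". Statistical Analysis turns this into a causal question: "a mediation analysis will be performed to determine whether sleep improvements following web-based CBT-I are the result of changes in sleep-related beliefs" or of other factors. The tool is named, but not the predictor, mediator and outcome: "Mediation analysis will be carried out using the bootstrapping method in the Hayes Process Macro for mediation, moderation, and conditional analysis for SPSS".

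Under Design and Procedure, one questionnaire battery contains both the candidate mediators (such as the DBAS-16, the Pre-Sleep Arousal Scale and the Glasgow Sleep Effort Scale) and the self-reported outcomes (the Pittsburgh Sleep Quality Index and the Insomnia Severity Index). It is given at baseline and after the program. Actigraphy and diary are taken at the same two stages. No mid-treatment mediator reading or later outcome follow-up is described.

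**The concern.** A claim that treatment works through a mediator needs three things: a contrast in treatment, a change in the mediator that can be placed before the change in the outcome, and some protection against common causes of both. This design has no treatment contrast and no such ordering, and without a control arm it has little protection against common causes.

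Mediation of CBT-I is a stated purpose in the Abstract's Objective and again in the Discussion's Conclusions, so this is not a side analysis. If the plan is followed as worded, anything that moves beliefs and sleep together can be reported as a mechanism of CBT-I. The article supplies one such candidate itself. Its Expected Findings section cites work linking changes in older adults' self-reported sleep during the COVID-19 pandemic mainly to changes in dysfunctional sleep beliefs, and this trial recruited from March 2020 to March 2021.

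**Working it through.** The article gives no figure for the mediation analysis, so there is nothing to reproduce. There are three checks.

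**1. Is there a treatment path to estimate?** The Introduction's hypothesis makes CBT-I the predictor X and sleep the outcome Y. A standard PROCESS mediation model fits

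- M = i₁ + aX + e₁
- Y = i₂ + c′X + bM + e₂

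and takes the indirect effect as a × b. With X = 1 for all 65 participants, the X column equals the intercept column, and the design matrix (intercept, X) has rank 1 instead of 2. Neither a nor the effect of X on Y is identified. With sleep group as X the model does run, but a × b then describes how far group differences in outcome travel through M.

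**2. Can change in the mediator be placed before change in the outcome?**

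| Measure | Occasions |
|---|---|
| Candidate mediators (questionnaires) | Baseline; after program |
| Self-reported sleep outcomes (same battery) | Baseline; after program |
| Actigraphy and diary | Baseline; after program |

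Each variable has one change score over the same interval. At baseline the questionnaire comes shortly before actigraphy, but that offset does not order the two changes. The Pittsburgh index looks back over a month and the program is to be completed within 4 weeks. The post-treatment outcome window therefore reaches back over much of treatment, to before the post-treatment mediator reading.

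**3. How often would a shared cause look like mediation?** Inputs from the article: n=60 (planned minimum) and n=65 (completed both phases). Assumed inputs: mean change of 0.5 SD in both mediator and outcome, change-score correlation r arising only from a shared cause, no effect of mediator on outcome, two-sided 5% tests. Mediation is declared when the mean mediator change differs from zero *and* the slope of outcome change on mediator change is significant. This joint test stands in for the bootstrap interval. Results from 3,000 simulated trials per setting:

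| r | n=60 | n=65 |
|---|---|---|
| 0 | 4% | 5% |
| 0.2 | 32% | 34% |
| 0.3 | 62% | 67% |
| 0.4 | 86% | 89% |
| 0.5 | 96% | 97% |

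Hand check at n=60, r=0.4:

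- Slope: atanh(0.4) × √57 = 0.4236 × 7.550 = 3.198, and Φ(3.198 − 1.96) = 0.892.
- Mean mediator change: 0.5 × √60 = 3.873, and Φ(3.873 − 1.96) = 0.972.
- Product: 0.892 × 0.972 = 0.867, close to the simulated 86%.

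Reversing the direction, so that improved sleep changes beliefs (standardized coefficient 0.4, same mean changes, no effect of beliefs on sleep), gives a declaration in 86% of trials at n=60 and 90% at n=65. The test responds almost identically to a shared cause and to reverse causation.

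**The case against.** The strongest reply is that Statistical Analysis names the macro but no X, M or Y. Model specification is commonly left to a fuller protocol or analysis plan, and comparing CBT-I outcomes between sleep groups is itself a phase 2 aim. This stands in part. A reader might infer that PROCESS cannot be run at all; the documents do not support that. The defect is that no choice of X available in this design answers the stated question. A fuller plan would not cure it, because the design and the causal aim are both fixed in this article and conflict.

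Other tempting readings also go too far:

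- **The simulated percentages as this trial's error rate.** They depend on correlations and mean changes that the article does not give. Power for the slope alone is higher (89% at n=60, r=0.4), but an indirect effect needs both paths, so the joint figures are the fairer ones.
- **A 30% to 37% chance of at least one false path across seven to nine mediator scores.** That is 1 − 0.95⁷ to 1 − 0.95⁹ and assumes independent scores. These are related scales from one battery, so independence is implausible.
- **Chronotype can only be a moderator.** The article does not say that chronotype is fixed. The scale asks about preferred sleep and wake times, and the program restricts time in bed. Its role as a mediator is unargued, not disproved.
- **Item overlap invalidates the analysis.** The basis is one DBAS-16 example item about worry and one description of the Insomnia Severity Index as covering "impairment of daytime functioning, and worry about sleep over the past 2 weeks". The article never names that index as the mediation outcome, and actigraphy is available.

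It is also fair that mediation is introduced as a further aim, and that Expected Findings speaks more softly of factors playing a role. The unqualified causal wording in Statistical Analysis remains.

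**Conclusion.** The point holds as a mismatch between aim and design. With one arm, identical treatment and two shared measurement occasions, the trial cannot show that improvement after CBT-I results from changed beliefs or any other listed factor. It can show whether people whose beliefs changed more also had larger changes in sleep.

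The identification argument rests only on what the article states. The size is illustrative: with moderate shared-cause correlations (0.3 to 0.4) and the assumed mean changes, false declarations would be the usual result at the trial's sample size. Even at 0.2 they occur in about a third of trials. What will actually be reported cannot be known from the article. The wording needs correcting before phase 2 conclusions are drawn, because the plan as written leads to an unsupported one.

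**What to change.** - **Model.** For each candidate factor, regress change in the sleep outcome on change in the factor, adjusting for the baseline values of both. A two-occasion within-person mediation model is an alternative only if labelled non-causal, since it still confounds CBT-I with time and regression to the mean. Name X, M and Y in either case.
- **Outcomes.** Include the actigraphy outcomes already collected, so that the result does not rest on self-report alone.
- **Wording.** In the Abstract's Objective, the Introduction, Statistical Analysis and the Discussion's Conclusions, replace mediation and result-of language with a statement that change in the factor is associated with change in sleep. Add that the design cannot attribute the change to CBT-I or establish its order.
- **Chronotype.** Justify it as a mediator or treat it as a baseline effect modifier.
- **Primary mediator.** The article says that phase 2 analysis was finalized in July 2022, so label any primary mediator chosen now as post hoc.

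The cost is re-analysis and rewording, with no new data. The conclusion becomes weaker but supportable. A causal mediation claim would need a concurrent control and mediator readings during treatment, which means a different trial.

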The Self-Efficacy for Sleep Scale [37] assesses the “belief people have in their ability to participate in certain behaviors needed to promote their health” [46,47]. The Self-Efficacy for Sleep Scale is a 9-item measure of how confident an individual is to carry out a variety of behaviors related to sleep, for example, “fall asleep at night in less than 30 minutes.” Items are scored on a 5-point scale, with higher scores being indicative of increased sleep self-efficacy. The SES has fair internal consistency (Cronbach α=.71) [48].

The Sleep Locus of Control Scale [38] is an 8-item measure that examines the internal sleep locus of control, the belief that sleep outcomes are dependent on one’s behavior on a 6-point Likert scale. The Sleep Locus of Control Scale contains 2 subscales, internal locus of control and chance sleep locus, and is reported to have internal consistency of Cronbach α=.72 (internal locus of control) and .59 (chance sleep locus) [38].

Hyperarousal will be assessed using the Pre-Sleep Arousal Scale (PSAS) [35]. The PSAS measures cognitive and somatic symptoms of arousal before falling asleep using 2 subscales. The 2 subscales each consist of 8 items. The items are rated using a 5-point Likert scale, with scores ranging from 1 to 5. The internal consistency of the PSAS has been reported as Cronbach α=.67 for the cognitive and .84 for the somatic subscales in normal sleepers and .76 and .81, respectively, for individuals with insomnia.

The Morningness-Eveningness Questionnaire [40] assesses chronotype. The 19-item scale was developed to examine individuals’ alertness at specific times of the day. The 19-item scale examines preferences in sleep and wake times and what times of the day subjects feel most alert. The Morningness-Eveningness Questionnaire has shown sufficient internal consistency for the original (Cronbach α=.82) as well as for the reduced version [49].

The Sleep-Related Behaviors Questionnaire [39] is a 32-item instrument that assesses safety behaviors relating to sleep; for example, “I miss or cancel appointments (daytime or evening).” Items are rated on a 5-point scale ranging from 0 (meaning “almost never”) to 4 (meaning almost always”). The questionnaire has high internal consistency (Cronbach α=.92).

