### Procedure

Participants who express an interest in participating will be contacted to make an appointment for a screening call. During the screening call, potential participants will be provided with information about the study and will be assessed against the eligibility criteria. Once a potential participant is confirmed to be eligible, they will complete, sign, and return the consent form. Upon study commencement, potential participants will be provided with an individual web-based link to the Qualtrics questionnaire battery (Qualtrics XM Platform software, Qualtrics). Once the questionnaire has been completed, actigraphs will be posted to participants using a courier service. Delivery and collection times will be arranged before dispatch at a time convenient for the participant. Where courier services are not available, the sleep watches will be posted by registered express mail, including a prepaid self-addressed return envelope. Study participants will be required to wear an actigraph on their nondominant wrist for 96 hours, except when they take a bath, have a shower, go swimming, or undergo any other activity that would result in them submerging the actigraph in water. They will also be instructed to record the exact time when they remove the actigraph and, subsequently, when they reattach the actigraph to their wrist in their sleep diary. This allows for accurate matching of the actigraph-estimated wear and nonwear times with the sleep diary. The sleep diary will be completed concurrently to record bedtimes, sleep and wake times, frequency and duration of nocturnal awakenings, rise times, daytime naps, and nonwear times, and will be returned with the actigraph after the measurement has been completed. A printed copy of the sleep diary will allow the participant to keep the diary on their bedside table so the relevant sections can be completed upon going to bed and waking up in the morning.

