### Description of Intervention

There are a variety of web-based CBT-I courses, mostly developed in the United Kingdom or the United States. One exception is the “This Way Up—Managing Insomnia” program [55,56]. This treatment course was created by a team of clinical psychologists and psychiatrists at the Clinical Research Unit for Anxiety and Depression, which is run by the University of New South Wales and St Vincent’s Hospital in Sydney. The free self-help program consists of 4 lessons in a comic-based format. Lesson 1 provides background knowledge about sleep and insomnia and which factors are conducive to good sleep and which ones are related to insomnia (sleep hygiene). Lessons 2 and 3 address the management of thoughts and behaviors that interfere with sleep (sleep restriction, stimulus control, and cognitive therapy). The sleep restriction protocol aims at decreasing nighttime awakenings by limiting the time a person spends in bed [57]. Initially, the prescribed time in bed corresponds with the average total sleep time as measured in the week prior to initiating the sleep restriction protocol, with a minimum time in bed of 5.5 hours. Time in bed is then gradually increased until the amount of nighttime sleep achieved is sufficient for individual requirements. Lesson 4 focuses on relaxation techniques. The program cannot be individually tailored to the patient’s specific sleep difficulties but provides broad topic coverage of the most common factors present in insomnia (eg, waking too early), and program participants are advised that not all themes covered may be relevant to their circumstances.

Each lesson takes about 20 minutes to complete, with additional compulsory homework. A unit only registers as completed once the homework has been downloaded. It is recommended that a user completes 1 lesson every 1-2 weeks. However, the system will not grant access for less than 5 days between modules. Reminders are emailed or sent by text message automatically once a new session becomes available, and there is also the option to set a web-based appointment for the next course module. In addition to the course unit and homework, participants are required to complete a sleep diary. Upon completion of the course, an extra 12 months’ access is made available for additional practice. The program is available only to individuals who live in Australia.

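### The named mediators are all questionnaires; change in time in bed, which the programme prescribes and the diary can measure, is not among them, so its effect can be credited to beliefs, effort or arousal

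*Protocol article*

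**What the plan says.** The Objective in the abstract undertakes to "examine the role of cognitive, behavioral, and hyperarousal processes in mediating the treatment outcomes of web-based CBT-I". The Statistical Analysis section puts the aim causally: to find out "whether sleep improvements following web-based CBT-I are the result of changes in sleep-related beliefs or other factors", by bootstrapping in the PROCESS macro.

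The mediators named are sleep-related beliefs (Statistical Analysis) and a further set in the Introduction: hyperarousal, sleep effort, self-efficacy, and "sleep locus of control [38], sleep-related behaviors [39], and chronotype [40] mediate the relationship between web-based CBT-I and sleep outcomes". The Design section gives a questionnaire for each. The one behavioural measure "is a 32-item instrument that assesses safety behaviors relating to sleep".

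On the intervention, the Description of Intervention states: "The sleep restriction protocol aims at decreasing nighttime awakenings by limiting the time a person spends in bed". Number of night-time awakenings is also one of the actigraphy outcomes (Design; Statistical Analysis).

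On data, the Procedure section states: "The sleep diary will be completed concurrently to record bedtimes, sleep and wake times, frequency and duration of nocturnal awakenings, rise times". The diary is repeated after treatment. The Statistical Analysis section gives it one use, as a check on the actigraphy scoring. Time in bed is named nowhere as a mediator or covariate.

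**The concern.** The article describes a direct behavioural route from programme to outcome and collects the data to measure it, but does not list it among the mediators. The trial has a single arm, so any mediation result rests on how changes vary together between participants. Those who follow the programme more closely could plausibly both restrict time in bed more and change their beliefs, effort or arousal more. With time in bed outside the model, the path from a questionnaire mediator to sleep then absorbs part of the restriction effect. Bootstrapping does not help, because it puts an interval around a confounded estimate.

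At stake is the sentence the analysis is meant to support. The abstract's Conclusions hope the results will help tailor CBT-I to individuals, and crediting the wrong component would misdirect that.

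**Working it through.** The article gives no mediation figure to reproduce. Its sample size (40, raised to at least 60) concerns group differences. The check is how far the omission could mislead.

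**Inputs.** N = 60 is the recruitment target in Statistical Analysis. Path strengths are assumptions over a range, as the article gives none.

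**Set-up.** All variables are standardised changes: T is change in time in bed, M a questionnaire mediator, Y sleep. T affects M with path a and Y with path c. M has no effect on Y.

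**Step 1: time in bed left out.** The spurious correlation of M with Y is a × c. By Fisher's z, the two-sided 5% test has mean atanh(ac) × √(N − 3), with √57 = 7.550. For 0.3 and 0.4: ac = 0.12, atanh = 0.1206, 0.1206 × 7.550 = 0.910. The chance of exceeding 1.96 in either direction is about 15%.

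| a / c | ac | mean z | false-positive rate |
|---|---|---|---|
| 0.2 / 0.2 | 0.04 | 0.30 | 6% |
| 0.3 / 0.4 | 0.12 | 0.91 | 15% |
| 0.4 / 0.5 | 0.20 | 1.53 | 33% |
| 0.5 / 0.6 | 0.30 | 2.34 | 65% |

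Simulation of 20,000 trials per setting agrees (6%, 15%, 34%, 65%). A percentile bootstrap of the indirect effect, closer to the planned method, gave 17%, 34% and 70% in the last three rows (600 data sets, 1,000 resamples each).

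**Step 2: time in bed added, measured without error.** The partial correlation of M and Y given T is zero, and the rate returns to about 5%. The bootstrap gave 6%, 6% and 9%.

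**Step 3: time in bed added, measured with error.** If observed change in time in bed has reliability ρ, the partial correlation is ac(1 − ρ) / √[(1 − a²ρ)(1 − c²ρ)]. For 0.5 and 0.6 with ρ = 0.5: 0.15 / √(0.875 × 0.82) = 0.15 / 0.847 = 0.177. The test mean is atanh(0.177) × √56 = 1.34, so the rate is about 27%.

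| a / c | ρ = 0.7 | ρ = 0.5 | ρ = 0.3 |
|---|---|---|---|
| 0.3 / 0.4 | 6% | 8% | 10% |
| 0.4 / 0.5 | 8% | 13% | 20% |
| 0.5 / 0.6 | 14% | 27% | 42% |

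These reliabilities are assumptions too. Error is likely here: each diary covers 96 hours, the second comes after the programme, and the Description of Intervention says time in bed is increased again after the initial limit.

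**Step 4: the reverse order.** Suppose belief change leads people to restrict (M to T, path a) and restriction improves sleep (T to Y, path c). The correlations among T, M and Y are then the same as in step 1: a, c and ac. M is significant in 15%, 33% and 65% of trials without T and in about 5% with it, but now the result without T reflects a real indirect effect. Changes over one interval cannot tell the two orders apart.

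**The case against.** The strongest objection is that not naming a variable is not the same as excluding it. The Introduction offers its list as examples, the analysis aim allows for other factors, and a condensed article leaves model details to a fuller plan. That stands to this extent: a reader might infer that time in bed has been ruled out, or that the analysis will name beliefs as the mediator, and the article supports neither. It does not say whether models are single or parallel or which covariates enter, and the rates above are possibilities under assumptions. The text nevertheless points away from time in bed: the Introduction closes by saying that the listed processes will be examined, and the Discussion speaks of beliefs, arousal and other cognitive factors.

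A second objection is that a behavioural mediator is already included, and that stimulus control and relaxation could be raised in the same way. The Objective is indeed met formally. But a safety-behaviour scale does not measure time in bed, and for sleep restriction the article itself both states the route to an outcome and collects the data from which it can be derived.

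A third objection concerns the remedy. A reader might infer that adding time in bed cures the problem, or that beliefs should be credited only if their path survives. Steps 3 and 4 show otherwise: adjustment is partial under measurement error, and a survival rule would discard a real effect that runs through time in bed. Both limits stand. So does the wider one: with a single arm, and with mediator and outcome changing over the same interval, causal mediation is not identified with or without this variable.

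**Conclusion.** The concern holds in limited form. The article states that restriction acts through time in bed, its diary allows change in time in bed to be derived, and its named mediators leave that change out, so an effect of restriction can be credited to a questionnaire construct. At N = 60 the distortion ranges from negligible (about 6% at 0.2/0.2) to serious (65% at 0.5/0.6). This rests on assumed path strengths and on time in bed driving both changes, neither of which the article establishes. Change in time in bed belongs in the analysis as a check on interpretation. It cannot decide by itself whether beliefs matter.

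**What to change.** - Derive each participant's mean diary time in bed (rise time minus bedtime) at baseline and after treatment, and add the change as a candidate mediator.
- Report each questionnaire mediator's path with and without it.
- If a path shrinks when time in bed enters, claim no effect of that mediator separate from sleep restriction, but do not rule the mediator out.
- Replace the wording about what improvements result from with wording about association, and give the single arm and the shared interval as the reasons.
- State that the diary after the programme may understate the restriction applied, so adjustment is partial.

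The cost is one derived variable from data already collected, one more parameter per model, and some rewording. The article says the phase 2 analysis was finalised in July 2022, so this would be a supplementary analysis or, at the least, a qualification of the reported conclusions.
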